**Fig. 3 Fig3:**
[figure not shown]
Template of SPIRIT recommended content for the schedule of enrolment, interventions, and assessments

Disincentive students received a gift card of $30 for participating in the study. Students who participated in all data gathering phases (2 times) received a gift card of $50 at follow-up. Students accessed SAML and substance abuse prevention education until the end of the semester.

#### Delayed-intervention group

Students in the delayed-intervention group received lessons during the study, but educators were requested to abstain from any substance abuse or SAML topics. Simultaneously, educators in the delayed-intervention group did not train them until after study completion (i.e., collecting student data at a 3-month follow-up).

#### Implementation procedure

As mentioned previously, participants in this study were familiar with e-learning classes and online education due to the COVID-19 pandemic. Educators accessed the web-based educator’s control panel, giving them access to programs. The principal investigator and the research team visited the website. Privacy shields were provided to block their computers or tablet screens from view to ensure confidentiality. Secret ID numbers were used in place of names in chat rooms, and during receiving education programs, admin and educator sessions were offered to students before education. Students were instructed that they could withdraw from the study at any time for any reason. Follow-up questionnaires were completed with paper copies of the pretest questionnaire. After completing the data collection, educators in the intervention group provided substance abuse prevention and SAML education over 3 weeks. It was predicted that the program could be completed in 5 45-min sessions. In the follow-up period, students in the intervention group gave their feedback on the program. Educators returned all completed follow-up questionnaires to administer and Principal Investigator after approximately 3 months. After collecting the follow-up data, educators in the delayed-intervention group could provide SAML and substance abuse prevention education to students and give feedback on their experiences.

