### Processes

#### Schools of university

First, university permission to conduct the study was obtained. University administrators would access questionnaires for an estimate if demanded. Efforts were made to balance the inclusion of both state and non-state universities, as well as to range in their socio-demographic characteristics. Based on the previous formative research [27] and random sampling of Hamadan universities, 3 universities were expected to participate. Therefore, the number of students in each school or university was obtained by proportional assignment of students to the school (i.e., the school with the largest number of students, the largest number of students assigned). After coordinating with university officials, the research units were rationed. Then, the samples were randomly collected.

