#### The intervention description

As noted based on the previous formative-mixed methods research, materials, the content of interventions, and the type of delivery channel to participants (which was based on audience tendencies) were identified and developed, and interventional education was developed by an interdisciplinary group consisting of specialists in psychology, media research, web site development, multimedia design, and health education and promotion.

SAML and preventive substance abuse educations were web-based and comprehensive education programs for university students, providing appropriate and medically accurate information about substance abuse using a media literacy education approach. It should be noted that this interventional education would be web-based because of the COVID-19 pandemic to comply with health protocols in Iran. Some advantages of this approach are as follows: Because of the COVID-19 pandemic and social-distancing measures in Iran, it is not clear when universities can return to normal education situations and face-to-face educational interventions. Thus, a web-based approach to delivering education interventions in person was selected. Also, this approach allows for a fully interactive environment or 2-way forms of communication, often between individuals who know each other (e.g., friends) and may have a strong influence on behavior. Moreover, the health of participants is valuable and important for all researchers.

Also, the web-based channel was based on audience preferences and provided more access to materials for interventions. This channel is more flexible, and students can access it at all times and any place, and any individual concerning personal conditions can educate and use educational materials.

Some disadvantages of this approach are as follows: access to comprehensive materials and support can be difficult, and this approach requires additional training before starting educational interventions.

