The pairing of preventive substance abuse information and SAML education allows the program to teach students critically thinking about media messages related to substance abuse specifically marijuana and substance abuse behaviors. It mostly teaches them what lifestyles, values, and points of view are represented in or omitted from media messages about substance abuse, such as identification and the possible implications of actual consumption of drugs, including simulating an actor, having instant excitement, believing in the non-addictive nature of advertised substance, and having ideal moods and herbal and not harmful effects.

Education consisted of 5 web-based education sessions about substance abuse prevention and SAML. Each session included 40–45 min of training with the question-and-answer methods. Group discussions (chat rooms) were held with multimedia tools and reminder messages, such as the first educational session to familiarize students with drugs, especially marijuana and substance abuse behavior consequences. The second session aimed to educate students on SAML skills, critical thinking, and media consumption regime. The third session aimed at familiarizing students with interpersonal skills and self-awareness, and the fourth session taught students how to say no and how to solve problems. The fifth session corrected students’ beliefs and attitudes toward substance abuse using the mentioned web-based teaching methods and materials—each containing group discussion in chat rooms. The intervention group received lessons between completing the pretest and follow-up (Fig. 3). The website contained an educator dashboard for educators. They will be one of the research teams to enroll the students in the program and group discussions, including chat rooms, to correct their beliefs about drugs. Educators were also allowed to use web-based education programs in order to make education programs more accessible to students. All educators were requested to review all of the materials.

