### Measures

#### Student measures

Students completed questionnaires at 2-time points: a pretest and a 3-month follow-up (Fig. 1). The student questionnaire, containing approximately 100 items, covered substance abuse behavior based on PWM variables outcomes (e.g., attitudes, normative beliefs, behavioral intentions, and willingness), self-reports of the SAML Scale (SAMLS), and process evaluation. In addition, demographic questions comprised age, education level, socioeconomic status, sex, gender, parental education level, marital status, name of university, schools and courses, history of smoking and alcohol consumption, addiction status in parents, close friends, substance abuse status, internet access, amount of social media exposure and use of social media, and motivation to use social media.

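### The only post-baseline outcome is collected on paper and returned through the educators who teach the programme, with no safeguard specific to the paper forms

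*Protocol article*

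**What the plan says.** **How follow-up is collected.** Under Implementation procedure, the article states: "Follow-up questionnaires were completed with paper copies of the pretest questionnaire". The same section gives the return route: "Educators returned all completed follow-up questionnaires to administer and Principal Investigator after approximately 3 months".

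**Who the educators are.** The intervention description says of them: "They will be one of the research teams to enroll the students in the program and group discussions". It adds that these discussions are meant to put right students' ideas about drugs. Implementation procedure speaks of educators in the intervention group and educators in the delayed-intervention group. The latter are asked to keep off these topics until follow-up is complete.

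**What the form holds.** Student measures describes about 100 items at pretest and at 3 months. They cover the prototype willingness constructs, the media literacy scale and personal items that include "history of smoking and alcohol consumption, addiction status in parents, close friends, substance abuse status". Age, sex, marital status, university, school and course are also asked.

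**Why teaching is online.** The intervention description says "this interventional education would be web-based because of the COVID-19 pandemic to comply with health protocols in Iran" and adds: "Moreover, the health of participants is valuable and important for all researchers". It also gives a reason unrelated to infection: "the web-based channel was based on audience preferences and provided more access to materials for interventions".

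**Confidentiality.** The article describes:
- privacy shields for screens (Implementation procedure);
- ID numbers in chat rooms and for receiving the programme (Implementation procedure; Oversight and monitoring);
- a secure server for the list of names and IDs (the retention section, Oversight and monitoring, Confidentiality);
- participant data without names (Sample size and eligibility criteria);
- a check by the Principal Investigator on coding, security and storage (Confidentiality).

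Schools of university adds: "University administrators would access questionnaires for an estimate if demanded".

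**The concern.** Two features of the stated procedure pull against the rest of the design.

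The first is who handles the outcome. Attitude, intention, willingness and substance use are all self-reported. A student who knows that the form goes back through the person who taught the sessions may lean towards the taught answer or leave out use. Intervention students have had that teaching by follow-up and delayed-intervention students have not, so the pressure need not be equal between arms. If it is unequal, it biases the between-group comparison, and the natural direction favours the intervention.

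The second is confidentiality. The form combines sensitive answers with several indirect identifiers. The measures the article describes in detail protect other things, and nothing is said that is particular to completed paper forms on their way from student to educator to administration.

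The mode is also hard to square with the rest of the trial. Internet access is an inclusion criterion, students are described as used to online classes, and there is a study website and a participant ID. The article gives no reason for collecting the outcome on paper.

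**Working it through.** No figure in the article bears on this point, so there is none to reproduce. The check sets the sections side by side and then writes out what each collection route does to the planned comparisons.

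**1. Is there another assessment to fall back on?** No. Student measures gives two time points, pretest and 3 months. Follow-up is the only post-baseline measurement.

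**2. Does any stated safeguard reach the paper form?**

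| Safeguard | What it covers | Specific to paper forms? |
|---|---|---|
| Privacy shields | Computer and tablet screens | No |
| ID numbers instead of names | Chat rooms and the education programme | No |
| Secure server | The list linking names to IDs | No |
| Data without names | Participant data in general | General only |
| Principal Investigator's check | Coding, security and storage in general | General only |

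**3. Does a form without a name settle confidentiality?** Not fully, for two reasons. The within-group paired tests under Statistical methods need each follow-up form matched to its pretest, so forms must carry a link of some kind. The personal items also narrow the field. With 116 students and the three universities expected, the average is 116 / 3 ≈ 39 students per university, before any split by school, course, age, sex or marital status. Cell sizes below that cannot be computed because the numbers per school and course are not given. This step takes the follow-up form to repeat the pretest's personal items, as the description of it as a copy of the pretest implies.

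**4. What does return through educators do to the between-group comparison?** Let the true follow-up means be μ_I and μ_C, and let the reporting shifts caused by the return route be b_I and b_C. The expected observed difference is

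(μ_I + b_I) − (μ_C + b_C) = (μ_I − μ_C) + (b_I − b_C).

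The bias is b_I − b_C, which vanishes only if the shifts are equal. The article gives no information on either.

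**5. What would an online follow-up do?** Suppose the pretest was on paper and the change of mode shifts answers by d in both arms.
- Between groups: (μ_I + d) − (μ_C + d) = μ_I − μ_C, so the shift cancels.
- Within a group: (μ_post + d) − μ_pre = (μ_post − μ_pre) + d, so the shift stays.

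The cost therefore falls on the paired comparisons. If the pretest was completed online, the present plan already has a mode change and online follow-up would remove it. The article does not clearly state the pretest mode.

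**The case against.** The best defence is that paper self-completion is a legitimate mode and that the stronger criticisms go beyond the text. Much of that stands.

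- **COVID-19.** A reader might infer that paper follow-up undoes the protection that web teaching gave. The article does not support this. It applies the pandemic rationale to teaching, gives other reasons as well, and never says that forms were handed over in person. Post or another low-contact route is not excluded. One questionnaire also does not cancel the benefit of moving five sessions online.
- **Exposure of named answers.** A reader might infer that identifiable drug-use answers reach outsiders. That is not shown. Educators are described as part of the research team and data as nameless. What remains is indirect identification and candour.
- **The secure server.** It is stated to hold the name and ID list, not the answers, so paper does not breach that assurance. Answers sent to the same place as the list could even weaken it, and the fix has to avoid that.
- **Attrition.** A reader might infer that closed universities mean lost forms. The article gives no basis for this. It provides a gift card for completing both data collections and two contacts with anyone who withdraws.
- **Condensed article.** Details of distribution may sit in the full protocol. That is fair, so silence on them is not the point. The point is the route that the article does state.

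The defence does not answer that route. Membership of the research team does not make educators neutral handlers, because they deliver the intervention. Postal distribution would not help either, since completed forms still go back through them. Administrators' access to questionnaires is a separate matter that online collection alone would not resolve.

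**Conclusion.** The point holds in a limited form. The article sends its only post-baseline self-report, on paper, back through the people who teach the programme, and the safeguards it spells out do not specifically cover those forms. This is an avoidable weakness in outcome collection and an uneasy fit with both the web-based design and the confidentiality assurances. It is not a demonstrated breach or a demonstrated bias.

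Its scope is every follow-up form in both arms, 58 per arm and 116 in all if everyone responds. Its effect on the estimate is b_I − b_C, which the article does not allow anyone to size.

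The conclusion assumes that educators handle completed forms, as the return sentence says, and that they are the same people who run the sessions and chat rooms. It does not assume that they read the answers. The change is worth making because it is cheap and protects the one measurement on which every outcome comparison rests.

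**What to change.** Rewrite the follow-up part of Implementation procedure so that questionnaires do not pass through educators:

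1. Collect follow-up online under the participant ID, with the same form and procedure in both arms, submitted directly to the research data store.
2. Keep those answers separate from the list linking names to IDs.
3. Use the same mode as the pretest where possible, and state what the pretest mode was.
4. Where paper is used, have the form carry only the ID and be returned sealed to staff who do not teach.
5. In the same edit, state who may see completed questionnaires, and reconcile this with the provision for university administrators.

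**Cost.** One online form has to be set up. The study website is described with a dashboard, lessons and chat rooms but no survey function, so this is some work. If the pretest was on paper, there is a mode change, expected to be small and equal in both arms. It would affect the within-group paired comparisons more than the between-group ones, and the report should say so. If forms have already been collected by the stated route, the report should describe that route as a limitation.

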### Measures

#### Student measures

Students completed questionnaires at 2-time points: a pretest and a 3-month follow-up (Fig. 1). The student questionnaire, containing approximately 100 items, covered substance abuse behavior based on PWM variables outcomes (e.g., attitudes, normative beliefs, behavioral intentions, and willingness), self-reports of the SAML Scale (SAMLS), and process evaluation. In addition, demographic questions comprised age, education level, socioeconomic status, sex, gender, parental education level, marital status, name of university, schools and courses, history of smoking and alcohol consumption, addiction status in parents, close friends, substance abuse status, internet access, amount of social media exposure and use of social media, and motivation to use social media.

#### Outcome measures

Scales of substance abuse behavior based on PWM included the constructs of attitude, subjective norms, and behavioral willingness, as well as prototype and intents of behavior [32, 39]SAMLS includes 13 questions [29]Process evaluation checklist

Process evaluation included student satisfaction and availability of educational material. The quality of educational material was assessed using a 5-point Likert scale.

#### Plans to promote participant retention and complete follow-up

It should be noted that after obtaining informed consent, participants were randomly given ID numbers to be used in the education program. The list of names and ID numbers was confidentially kept on a secure server, only accessible to the principal investigator and administration staff (skilled in the ethical study). If any participant discontinued or withdrew from the education plan, administration staff would make efforts to encourage him/her to continue the study via 2 contacts.

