### Sample size and eligibility criteria

According to previous studies, the intervention’s minimum effectiveness is 20% [35–37], referring to changes in the PMW construct, behavior, and SAML. Also, because of considering these cultural differences in the intervention’s minimum level of effectiveness, 20% was considered for intervention effectiveness based on the previous study with the same field and approach; taking into account the clustering coefficient of 1.5, alpha 5%, and 90% desired power, we need 54 people per group. Also, considering the 20% probability of attrition in the intervention process, the present study’s sample size was 116, including 58 in the experimental group and 58 in the control group.$$n=\frac{\overline{p}\left(1-\overline{p}\right){\left({Z}_{\beta }+{Z}_{\alpha /2}\right)}^2}{{\left({p}_1-{p}_2\right)}^2}$$

Inclusion criteria were access to the internet and social media apps (such as WhatsApp, Telegram, and Instagram), being a student in one of the universities in the city of Hamadan, and willing to participate in the study. Before participation, students signed written informed consent forms to participate in this study. The Principal Investigator will access consent forms of student participant data that will be nameless. Also, according to the consent form, students were free to withdraw from the study at any time.

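### Retention contacts are triggered by leaving the education plan, which only intervention students have before the 3-month follow-up: a modest, cheaply removed risk of differential attrition

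*Protocol article*

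**What the plan says.** Under the heading on promoting retention and complete follow-up, the article states a rule: "If any participant discontinued or withdrew from the education plan, administration staff would make efforts to encourage him/her to continue the study". The effort is two contacts ("to continue the study via 2 contacts"). No other step there responds to a participant dropping out.

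The timing of the education is given elsewhere:

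- Intervention arm (The intervention description): "The intervention group received lessons between completing the pretest and follow-up".
- Delayed-intervention arm (Delayed-intervention group): students have lessons in which "educators were requested to abstain from any substance abuse or SAML topics", and "educators in the delayed-intervention group did not train them until after study completion". That section defines study completion as collection of the 3-month data.
- Implementation procedure: "After collecting the follow-up data, educators in the delayed-intervention group could provide SAML and substance abuse prevention education to students".

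One incentive is linked to the assessments and not to the lessons. It stands in the text after Fig. 3: "Students who participated in all data gathering phases (2 times) received a gift card of $50 at follow-up". It carries no restriction by arm.

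The sample size section allows for loss with the words "considering the 20% probability of attrition in the intervention process". It does not split that loss by arm.

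**The concern.** A control student who drifts away before the 3-month questionnaire has not left an education plan, because none has started for that student. Followed to the letter, the rule sends two contacts to intervention students who stop the lessons. It sends none to control students who are about to be lost. It also sends none to a student in either arm who finishes or ignores the lessons and then does not return the questionnaire.

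The analysis needs the 3-month questionnaire, whether or not the lessons were completed. If one arm is chased and the other is not, the arms can differ both in follow-up rate and in how many hard-to-reach students are among the completers. In a trial of self-reported substance use and intentions, non-responders may well differ on the outcome. The completers compared at 3 months would then no longer be balanced by randomisation, and the standard error would not show it. The Statistical methods section offers an unnamed imputation method if needed, which does not settle the matter.

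**Working it through.** **1. Who can meet the trigger before the outcome is measured?**

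- Trigger: discontinuing or withdrawing from the education plan.
- Intervention arm: the lessons fall between pretest and follow-up, so the trigger can be met.
- Delayed arm: the education comes after the 3-month data, so the trigger cannot be met while those data can still be lost.

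Two sentences might seem to say otherwise. The delayed arm does receive lessons during the study, but the Abstract shows that these are regular courses without the trial's topics. The Blinding description says that all members accessed the education, but it places the delayed arm's training after the post-test. The literal reading stands.

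**2. The article's own attrition figure.** It goes from 54 to 58 per group for 20% attrition. That does not reproduce: 54/0.80 = 67.5, so 68; 54 × 1.20 = 64.8, so 65; and 58 allows for only 1 − 54/58 = 6.9% loss. This is a separate matter. Below, the 20% serves only as an assumed loss rate without contacts.

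**3. Follow-up by arm.** Assumptions not in the article: unaided loss is 20% in both arms, and contacts recover a share r of it in the intervention arm only, with r from 1/3 to 1/2.

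- Control: 58 × 0.80 = 46.4, about 46 completers (80%).
- Intervention, r = 1/3: 0.80 + 0.20/3 = 86.7%; 58 × 0.867 = 50.3, about 50.
- Intervention, r = 1/2: 0.80 + 0.10 = 90%; 58 × 0.90 = 52.2, about 52.

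The difference of about 4 to 6 questionnaires is recovery forgone in the control arm. It is not loss on top of the 20%.

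**4. Shift in the completer comparison.** Let non-responders differ from responders by d SD (assumed 0.3 to 0.5). Recovered students move the intervention completers' mean by 0.2·r·d / (0.8 + 0.2·r), and the control mean does not move.

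| r | d | Shift (SD) |
|---|---|---|
| 1/3 | 0.3 | 0.020/0.867 = 0.023 |
| 1/3 | 0.5 | 0.033/0.867 = 0.038 |
| 1/2 | 0.3 | 0.030/0.900 = 0.033 |
| 1/2 | 0.5 | 0.050/0.900 = 0.056 |
| 1 (every non-responder recovered) | 0.5 | 0.100/1.000 = 0.10 |

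**5. Against sampling error.** With about 46 and 51 completers, the standard error of a difference in means is √(1/46 + 1/51) = 0.20 SD before any clustering. The range 0.023 to 0.056 SD is 0.11 to 0.28 of one standard error.

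**6. Direction.** Step 3 assumes equal unaided loss. Only the intervention arm carries five sessions of 40 to 45 minutes before follow-up, so its unaided loss may be higher. With control loss at 20%, one-sided contacts equalise the rates when unaided intervention loss is 0.20/(1 − 1/3) = 30% or 0.20/(1 − 1/2) = 40%. In such cases they narrow the gap in rates, although the mix of students retained could still differ.

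**The case against.** The strongest reply is that loose wording is being read as an operating rule. The sentence covers any participant, sits under a heading about complete follow-up, and asks staff to encourage the student to continue the study. The same section ties every participant's ID number to the education programme, so its education wording may simply stand for the trial. This has force: a study-wide intent is plausible. It does not remove the point, because staff act on the trigger as written. If both arms were meant, the sentence should say so.

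Second, a reader might infer that follow-up effort as a whole favours the intervention arm. The article does not support that. The $50 card rewards completing both assessments and is not limited by arm, and the delayed arm is offered the programme after follow-up. Only the drop-out-triggered contacts differ.

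Third, a reader might infer that control non-responders went unchased. No passage says so. The article condenses a fuller protocol, and reminder procedures are the kind of detail an article leaves out. What remains is narrower: the rule that is stated names an event that only one arm can experience in time.

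Fourth, the size is small and rests on assumed inputs, and the direction is open. Both are correct.

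**Conclusion.** The point holds in a limited form. As worded, the only retention step triggered by drop-out can reach intervention students alone before the 3-month data are in, and it is tied to the lessons and not to the questionnaire.

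This creates a risk of differential attrition; it does not show that any occurred. Under the assumptions above, the shift is about 0.02 to 0.06 SD, or roughly 0.1 to 0.3 of a standard error. The 0.10 SD ceiling would require two contacts to recover every non-responder. None of these inputs except the 20% comes from the article. The sign is not known in advance, and the contacts might even narrow a gap caused by lesson burden. It would therefore be wrong to conclude that the comparison is biased towards either arm, or that this alone could overturn a result. The priority is minor to moderate, and the case for acting rests mainly on the very low cost.

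**What to change.** Reword the retention sentence so that:

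- the trigger is an unreturned 3-month questionnaire, for any participant in either arm;
- the same two contacts are made on the same schedule in both arms;
- the contacts ask for the questionnaire even where the student has stopped the lessons.

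Report follow-up by arm with the results. The cost is one sentence and a few extra messages by the same administration staff. If data collection has already ended, the sponsor can still state who was contacted in each arm and give attrition by arm.
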